## Abstract

**Background:**

Poor memory for treatment is associated with poorer treatment adherence and poorer patient outcomes. The memory support intervention (MSI) was developed to improve patient memory for treatment with the goal of improving patient outcomes. The aim of this study protocol is to conduct a confirmatory efficacy trial to test whether a new, streamlined, and potent version of the MSI improves outcomes for midlife and older adults. This streamlined MSI is comprised of constructive memory supports that will be applied to a broader range of treatment content. The platform for this study is the Transdiagnostic Intervention for Sleep and Circadian Dysfunction (TranS-C). We will focus on midlife and older adults who are low income and experiencing mobility impairments.

**Methods:**

Participants (*N* = 178) will be randomly allocated to TranS-C + MSI or TranS-C alone. Both intervention arms include eight 50-min weekly sessions. Assessments will be conducted at pre-treatment, post-treatment, 6-, and 12-month follow-up (6FU and 12FU). Aim 1 will compare the effects of TranS-C + MSI versus TranS-C alone on sleep and circadian functioning, daytime functioning, well-being, and patient memory. Aim 2 will test whether patient memory for treatment mediates the relationship between treatment condition and patient outcomes. Aim 3 will evaluate if previously reported poor treatment response subgroups will moderate the relationship between treatment condition and (a) patient memory for treatment and (b) treatment outcome. Exploratory analyses will compare treatment condition on (a) patient adherence, patient-rated treatment credibility, and patient utilization of treatment contents, and (b) provider-rated acceptability, appropriateness, and feasibility.

**Discussion:**

This study has the potential to provide evidence for (a) the efficacy of a new simplified version of the MSI for maintaining health, well-being, and functioning, (b) the wider application of the MSI for midlife and older adults and to the treatment of sleep and circadian problems, and (c) the efficacy of the MSI for sub-groups who are likely to benefit from the intervention.

**Trial registration:**

ClinicalTrials.gov NCT05986604. Registered on 2 August 2023.

## Introduction

### Background and rationale {6a}

Patient memory for the content of treatment is poor. Only one third of recommendations made during physician visits are accurately recalled (e.g., [1–3]), and patients may recall *in*accurate information. Indeed, one study found that 25% of patients recalled treatment recommendations that had *not* been made [4]. Patients receiving cognitive and behavioral treatments have similarly poor memory for their treatment [3, 5]. Collectively, these findings are important because poor memory for treatment has been associated with poorer adherence [6–8] and poorer outcomes [3, 7, 9].

There are several explanations for why patient memory may be poor. First, even when memory is functioning optimally, memory can fail during the encoding and retrieval process [10]. Second, cognitive and behavioral treatment sessions are long, cover complex material, and can elicit negative emotions that bias attention and in turn bias encoding of information [11]. Third, patients may also struggle to transfer knowledge learned in therapy to real-world situations, known as the transfer of learning problem; in other words, they may struggle to recall applicable treatment skills and concepts in their everyday lives [12].

Promisingly, however, the impact of memory failures can be minimized at both the encoding and retrieval stages through the use of memory support strategies, which have been shown to be effective at improving memory in individuals with depression and Alzheimer’s disease [13–15]. Building on this prior research, the Memory Support Intervention (MSI) was developed to improve patient memory for treatment contents with the aim of improving patient outcomes [16]. In line with the Experimental Therapeutics Approach [17, 18], the MSI was designed to engage a target mechanism of change, *patient memory for treatment*, which is proposed to mediate patient outcomes [16]. The intervention was designed to improve memory for treatment contents rather than to improve general memory functioning. The original MSI consists of eight different memory supports that were derived from education and cognitive psychology research [19–22]. Four of the memory support strategies are *constructive*, defined as supports that prompt patients to generate new ideas, inferences, or connections in relation to treatment content. The other four memory support strategies are *non-constructive* and highlight aspects of treatment without asking patients to generate anything new related to it [16, 23]**.**

In a small pilot study (*n* = 48), adults with major depressive disorder (MDD) were randomized to receive either cognitive therapy plus the Memory Support Intervention (CT + MSI) or cognitive therapy as usual (CT-as-usual) [24]. Patient memory for treatment contents was enhanced in the CT + MSI condition relative to CT-as-usual at post-treatment with a small to medium effect size. Results from a confirmatory efficacy trial (*N* = 178) where patients diagnosed with MDD were also randomized to CT + MSI or CT-as-usual found improvements in the CT + MSI condition relative to CT-as-usual on only two secondary outcome measures: (1) lower depression severity at 6-month follow-up and (2) a greater reduction in unhealthy days from pre-treatment to 6-month follow-up [25]. A secondary analysis of this trial assessed differences at 12-month follow-up and did not find any significant differences in outcomes between the two treatment conditions [26].

There are several lines of evidence from other secondary analyses that indicate additional investigation is needed. First, the dose of memory support delivered in the trial may not have been sufficient to elicit significant improvements in patient memory or treatment outcomes [9]. Second, therapist use of memory support was indirectly associated with improved patient outcomes. Specifically, this effect was mediated by greater patient adherence to treatment recommendations as well as increased utilization and competency of CT skills, up to 1 year after treatment [27]. Third, therapists used most of their memory support for cognitively focused treatment contents including the cognitive model and cognitive restructuring which resulted in patients having improved recall of this information [26]. The latter point is of concern because it has been demonstrated that *procedural* treatment contents (e.g., practical intervention recommendations) are more closely related to patient outcomes than *conceptual* treatment contents (e.g., the underlying theoretical model used in treatment) [28]. Therefore, it is possible that greater therapist use of MS for procedural treatment content (e.g., behavioral activation) may be more effective than conceptual treatment content (e.g., the cognitive model). Training therapists to more adequately spread their use of memory support to a broader range of treatment content could strengthen the MSI. Fourth, constructive memory support strategies have been demonstrated to be more effective at improving patient recall relative to non-constructive strategies [23]. However, in prior research, there was not a sufficient focus on constructive memory support strategies, with therapists delivering non-constructive strategies twice as frequently as constructive [29]. Similarly, in the pilot study testing the MSI, therapists used non-constructive strategies four times more frequently than constructive strategies [30]. Given that constructive strategies appear to be more effective at improving memory for treatment, focusing on constructive memory support strategies may further strengthen the MSI. Taken together, these findings indicate that the MSI may engage important treatment mechanisms (e.g., adherence, skill competence, and utilization) that indirectly improve outcomes but could benefit from further investigation to engage the target of patient memory more effectively, which in turn, has potential to enhance the direct effect on patient outcomes [17].

In the paragraphs that follow, we will discuss how the present study will expand the evidence base on the MSI and test changes to increase its potency. The MSI was developed to be applied to a broad range of treatments (“pantreatment”) and to different mental disorders (“transdiagnostic”). As reviewed above, the MSI has so far only been tested for one mental disorder (major depressive disorder) and one type of treatment (CT) [25]. CT has been demonstrated to be an efficacious treatment that already has some memory support strategies embedded [31]. Therefore, further research is needed to evaluate the utility of memory support beyond CT alone, at a higher dose, and for a wider range of treatment content.

In the current study, the MSI has been streamlined to include only the most potent memory supports. The MSI was originally comprised of 8 different memory supports but has been simplified to include only the 4 *constructive* memory supports that prompt learners to generate new ideas, inferences, or connections that go beyond what is explicitly presented in treatment-as-usual. Findings have suggested that these strategies result in better learning, relative to passively absorbing information [23].

The current study also builds on prior research by investigating a broader application of the MSI. Specifically, we will recruit midlife and older adults who are experiencing problems related to sleep or circadian functioning. We focus on midlife and older adults for several reasons. As life expectancy increases, so does the aging population [32, 33]. Healthy aging is associated with declines in memory functioning [34–38]. This decline in memory functioning occurs during a period of life when there is often an increased need to utilize health services [39]. Considering evidence for the relationship between poor memory for treatment and poor treatment outcomes, coupled with reduced memory functioning and increased health care utilization in older individuals, improving patient memory for treatment, via the MSI, has been hypothesized to be highly impactful for midlife and older individuals [16].

The “platform” through which we will continue studying the MSI is a psychological treatment for sleep and circadian problems. This focus was selected because sleep and circadian disturbance is common among midlife and older adults [40–42]. For example, healthy aging is associated with decreases in total sleep duration, decreased sleep efficiency, increased sleep latency, and more frequent nighttime awakenings [43, 44]. Untreated sleep and circadian problems also have critical negative consequences including an increased risk for new onset of psychiatric and medical illness [45], increased accidents [46, 47], increased fall risk [48–50], increased chronic pain [51], and reduced physical activity [52].

Cognitive behavior therapy for insomnia (CBT-I) has been demonstrated to be an effective treatment for insomnia among midlife and older adults [53, 54] while also improving the symptoms of comorbid physical and mental disorders [55–58]. However, midlife and older adults experience a broader range of sleep and circadian dysfunctions (e.g., advanced circadian phase, medical problems, sleep apnea). To address this broader range, the current research will focus on the Transdiagnostic Sleep and Circadian Intervention (TranS-C) [59] as it incorporates the components of CBT-I, but also includes a range of content related to other sleep and circadian problems experienced by midlife and older adults. TranS-C is a modular, skills-based approach that is transdiagnostic in that it has been designed to address a range of sleep and circadian problems for a range of mental and physical disorders. Interestingly, in prior research, older people had a poorer response to TranS-C relative to younger people [60]. In another study limited to midlife and older adults, TranS-C was associated with improvements in many outcomes (depression, sleep disturbance, sleep health, and select sleep/wake outcomes), but not all improvements were sustained at follow-up [61]. The present study tests whether adding the MSI to TranS-C may further improve outcomes for midlife and older people.

Previous research has also demonstrated other sub-groups that have a poor response to treatment including individuals with fewer years of education [24, 62, 63], poorer baseline cognitive functioning [64, 65], and greater baseline symptom severity [66]. We will also examine if these poor response sub-groups will derive a particular benefit from adding the MSI to TranS-C.

From this population of midlife and older adults, we will also focus on recruiting individuals who are low-income and experience mobility impairments. We selected this focus as these are two problems that co-occur with aging [41, 67] yet are minimally studied [68–70]. Furthermore, there is an unmet need for health care for individuals who are both low-income [71–73] and have mobility impairments [71–73]. There is increasing scientific evidence supporting the use of telehealth in sleep and circadian medicine [74–76]. Therefore, the current study will deliver the MSI via telehealth to increase accessibility for this underserved population.

In summary, the overarching goal of the current study is to assess whether memory support strategies implemented into TranS-C can improve patient memory for treatment thereby improving patient outcomes among midlife and older adults. Over a 4-year period, midlife and older adults (*n* = 178, including 20% for attrition) will be randomly allocated to TranS-C + MSI or TranS-C alone and will be assessed at pre-treatment, post-treatment, 6-month follow-up (6FU), and 12-month follow-up (12FU). This is a randomized control trial that incorporates aspects of both Stages 2 and 3 of the NIH Stage Model [77]. Specifically, therapists affiliated with the research team will deliver the intervention to maintain the high level of control necessary to establish fidelity and internal validity (Stage 2). Participants will be recruited from community settings as a first step toward testing the delivery of the MSI in routine practice (Stage 3), bridging the gap between research and practice [78, 79].

### Objectives {7}

The first aim is to assess the efficacy of incorporating the MSI into TranS-C, compared to TranS-C alone. We hypothesize that compared to TranS-C alone, TranS-C + MSI will be associated with improvements in sleep and circadian functioning, daytime functioning, well-being, and patient memory at post-treatment, 6FU, and 12FU. The second aim is to evaluate if patient memory for treatment contents mediates the relationship between treatment condition and sleep and circadian functioning. We hypothesize that TranS-C + MSI will be associated with enhanced memory for treatment relative to TranS-C alone and enhanced memory for treatment will be associated with improvements in sleep and circadian functioning at post-treatment, 6FU, and 12FU. The third aim is to assess whether previously reported poor treatment response sub-groups will moderate the relationship between treatment condition and (a) patient memory for treatment and (b) treatment outcome, such that individuals in these sub-groups may derive a greater benefit from receiving memory support. It is hypothesized that treatment effects for those in the TranS-C + MSI condition will be larger at post-treatment for individuals who are older, have fewer years of education, poorer baseline cognitive functioning, and more severe baseline sleep disruption and sleep-related impairment. Exploratory analyses will compare treatment condition on (a) patient adherence, patient-rated treatment credibility, and patient utilization of treatment contents and (b) therapist-rated acceptability, appropriateness, and feasibility.

### Trial design {8}

This study is a parallel group, randomized, controlled, superiority trial. Participants will be randomized to TranS-C + MSI or TranS-C alone with a 1:1 allocation ratio.

## Method: participants, interventions, and outcomes

This study was preregistered on clinicaltrials.gov (identifier: NCT05986604). The study received approval from the Committee for the Protection of Human Subjects (CPHS) at the University of California, Berkeley (UCB). If there are too many findings to reasonably interpret in one paper, we may separate some of the findings into multiple papers. This research is funded by the National Institute of Aging (R01AG082651). See Fig. 1 for a flow diagram depicting the study design.

**Fig. 1 Fig1:**
[figure not shown]
Standard Protocol items: anticipated patient flow for randomized clinical trial

### Study setting {9}

A total of 178 adults who meet the eligibility criteria will be recruited within the USA. As sleep problems tend to be more prevalent in females relative to males [80, 81] and females tend to live longer than males [82], we plan to overrecruit females (65% females/35% males). Participants will be reimbursed $100 for each of the three post-treatment assessments, for a total of $300.

### Eligibility criteria {10}

#### Inclusion criteria

The inclusion criteria are:Aged 50 years and olderEnglish language fluencyExperiencing mobility impairment as determined by endorsing “mild”, “moderate”, “severe”, or “extreme or cannot do” on at least one item on the WHODAS 2.0 5-item “Getting Around” subscale [83], or “Yes” on at least one item of items 1–6 of the Adapted Brief Disability Questionnaire (BDQ) [84]Being part of a low-income household as determined by having a yearly household income below the Low Income Limit established by the US Department of Housing and Urban Development’s Fiscal Year Income LimitsExhibit a sleep or circadian disturbance as determined by selecting 4 (“quite a bit”) or 5 (“very much”), or the equivalent for reverse-scored items, on one or more of the PROMIS-SD items [85]A minimum score of 25 or above on the Montreal Cognitive Assessment (MoCA) as a negative screen for mild cognitive impairment [86]Willing and able to give informed consent

#### Exclusion criteria

The exclusion criteria are:Severe untreated sleep disordered breathing (apnea-hyponea index; AHI > 30) or moderate untreated sleep disordered breathing (AHI of 15–30) [87] with severe daytime sleepiness (Epworth Sleepiness Scale > 10) [88]. Individuals who screen positive for severe or moderate sleep disordered breathing and provide evidence for adherence to a non-study evidence-based treatment for obstructive sleep apnea (e.g., CPAP) will be eligible to move forward with the study (described in more detail in the screening measures below)Medical conditions that prevent a participant from comprehending and following the basic tenants of treatment (e.g., dementia) or that interfere with sleep in a manner that cannot be addressed by a cognitive behavioral treatment (e.g., the Structured Clinical Interview for Sleep Disorders will be used to screen for narcolepsy, REM sleep behavior disorder) or that may preclude full participation (e.g., receipt of end of life care) [89]HomelessnessNight shift work for more than two nights per week in the past 3 months (i.e., regularly scheduled work from 12 a.m. to 6 a.m.)Substance abuse/dependence if it makes participation in the study unfeasible. Participants are screened for use, amount and frequency of substance use using questions from the Mini-International Neuropsychiatric Interview (MINI) [90]Current suicide risk sufficient to preclude treatment on an outpatient basis (assessed via the Columbia-Suicide Severity Rating Scale) [91]

### Who will take informed consent? {26a}

The assessment team will be responsible for the informed consent process. During the recruitment period, verbal consent will be obtained prior to assessing inclusion and exclusion of potentially eligible patients. Written informed consent will be obtained prior to starting the pre-treatment assessment via HIPAA-compliant DocuSign or paper consent forms. All participants are informed that they can withdraw from the study at any time.

### Additional consent provisions for collection and use of participant data and biological specimens {26b}

The consent form covers all data collected. This trial does not include the collection of biological specimens.

## Interventions

### Explanation for the choice of comparators {6b}

Two variations of TranS-C are tested in the present research: TranS-C + MSI and TranS-C alone. Both treatment groups will complete eight 50-min sessions over 8–10 weeks.

### Intervention description {11a}

#### TranS-C alone

For the present study, TranS-C is comprised of 4 cross-cutting modules featured in every session, 5 core modules, and 8 optional modules that are used based on clinical presentation, treatment goals, and provider case conceptualization [59]. TranS-C modules have been modified and developed to address specific sleep and circadian challenges experienced by midlife and older adults. The *cross-cutting modules* are case formulation, education, motivational enhancement, and goal setting. *Core module 1* targets irregular sleep–wake times, difficulty winding down, and difficulty waking up. *Core module 2* aims to address poor sleep efficiency via stimulus control [92], sleep restriction [93], or sleep compression [94, 95]. *Core module 3* focuses on improving daytime function [96]. *Core module 4* aims to correct unhelpful beliefs about sleep [97]. *Core module 5* promotes the maintenance of change. *Optional module 1* helps participants reduce time in bed for people who are long sleepers. *Optional module 2* addresses delayed or advanced phase circadian problems (e.g., going to sleep later than desired or waking up earlier than desired). *Optional module 3* helps participants manage worries about sleep. *Optional module 4* promotes compliance with Continuous Positive Airway Pressure (CPAP) for participants with sleep apnea [98]. *Optional module 5* helps participants negotiate sleep in complicated environments (e.g., noise from bed/roommates, traffic noise, streetlight entering the bedroom). *Optional module 6* is for participants who experience nightmares [99]. *Optional module 7* is for participants who wish to taper from sleep medications [100]. *Optional module 8* uses problem solving to address sleep challenges for midlife and older adults (e.g., nocturia, chronic pain, medical problems) [101].

### *TranS-C* + *Memory Support*

The TranS-C + MSI condition is identical to the TranS-C alone condition with the exception that Memory Supports will be integrated without adding to the length of the session. Therapists in this condition will be trained to administer an average of 10–12 instances of constructive memory support per session. The rationale is that in our prior research, the optimal dose in which 75% of patients reached a clinically meaningful change ranged from 8 to 12. This dosage of 10–12 is meant as a conservative goal, given that the majority of outcomes were maximized with fewer than 10 memory supports per session [9].

The streamlined MSI used in this study is comprised of 4 constructive memory support strategies: evaluation, categorization, cue-based reminder, and application. Evaluation involves patients evaluating the benefits and drawbacks of a treatment point or comparing the point to an alternative, which promotes deeper processing and conceptual understanding [102, 103]. Categorization is where the participant groups information by higher-order categories, which has been shown to improve recall [104, 105] and increase memory capacity [106, 107]. Cue-based reminders encourage participants to utilize internal and external cues that increase the potential for transfer of knowledge from therapy to everyday life [108]. Application encourages participants to apply learned material in therapy to similar situations [109, 110].

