**Manipulation Checks**	
Memory Support	Memory Support Rating Scale (Total amount; Number of types)
Patient Memory	Patient Treatment Recall Task

*PROMIS-SD* PROMIS-Sleep Disturbance, *WHODAS 2.0* World Health Organization Disability Assessment Schedule, *PANAS SCISD* Structured Clinical Interview for Sleep Disorders, *ESS* Epworth Sleepiness Scale, *PROMIS-SRI* PROMIS-Sleep Related Impairment, *PANAS* Positive Affect and Negative Affect Schedule, *TARS* Therapist Adherence Rating Scale

**Table 2 Tab2:** SPIRIT depiction of tPliming of study measures

	**Screen**	**Pre-Tx**	**Tx Sessions**				**Post-Tx**	**6FU**	**12FU**
			**1–3**	**4**	**5–7**	**8**			

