### Therapist fidelity measures

#### Memory support

The *Memory Support Rating Scale* (MSRS) is a reliable and valid observer-coded measure that assesses the frequency and type of memory support used by treatment providers by analyzing treatment session video recordings [121]. MSRS coders are independent of the treatment provider and assessment teams and are masked to treatment condition. Coders will rate one randomly selected treatment session for each participant. Two measures are derived: the amount of memory support used per session and the number of different types of memory support strategies used per session.

The *Memory Support Treatment Provider Checklist* is a provider-rated measure of the use of the four memory support strategies that comprise the Memory Support Intervention for this study: Application, Categorization, Cue-based Reminder, and Evaluation. Therapists will rate the extent to which they delivered each memory support strategy in a given session on a 4-point scale: never (0 times), a few (1–2 times), often (3–5 times), and many (6 + times). These responses will be scored as never (0 times) = 0, a few (1–2 times) = 1, often (3–5 times) = 2, and many (6 + times) = 3. Two additional variables will be calculated: the total number of times memory support was utilized by summing the scores for each type of memory support on the scale (total number of memory supports used) and the total number of distinct memory support categories used out of a maximum possible total of four (total number of categories of memory support used). As the items on the scale are a range (e.g., 3–4 times), the total number of memory supports used represents a general estimate of memory support used, rather than a precise estimate. Therapists delivering MSI will complete this measure after each treatment session.

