### Fidelity checks

To assess therapist competence and fidelity to treatment, data from the Provider-Rated TranS-C Checklist, checklist of treatment elements specific to TranS-C, and the Memory Support Treatment Provider Checklist will be reported. The Memory Support Treatment Provider Checklist will be used to evaluate whether providers delivered the recommended dose of memory support.

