### Manipulation check

To check the assumption that the MSI will effectively result in the delivery of constructive memory support and manipulate patient recall during the TranS-C, independent samples *t*-tests will be used to assess if the total amount of constructive memory support, the different number of types of constructive memory support (measured by the MSRS), and patient recall will be greater in the TranS-C + MSI condition compared to TranS-C alone.

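### Delivered dose is judged from a therapist self-rating whose score is not on the scale of the 10–12 target, while the masked observer count is formally analysed only between arms

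*Protocol article*

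**What the plan says.** All places are in the protocol article.

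- **Target.** TranS-C + Memory Support: "Therapists in this condition will be trained to administer an average of 10–12 instances of constructive memory support per session". The same paragraph bases this on earlier work in which "the optimal dose in which 75% of patients reached a clinically meaningful change ranged from 8 to 12". It calls 10–12 a conservative goal, because most outcomes peaked below 10 supports per session.
- **Why dose matters.** Background and rationale {6a} says of the predecessor trial that "the dose of memory support delivered in the trial may not have been sufficient to elicit significant improvements in patient memory or treatment outcomes". The Discussion lists the higher dose among the trial's novel contributions.
- **Dose check.** Fidelity checks: "The Memory Support Treatment Provider Checklist will be used to evaluate whether providers delivered the recommended dose of memory support". Under Memory support (therapist fidelity measures), this checklist is self-rated after each session by the therapists delivering the intervention. Each of four strategies is coded 0 (never), 1 (1–2 times), 2 (3–5 times) or 3 (6 or more), and the codes are added. The article itself says the total is a general rather than a precise estimate.
- **Observer count.** The same section describes the MSRS, with one randomly selected session coded per participant: "MSRS coders are independent of the treatment provider and assessment teams and are masked to treatment condition". Table 1 lists it under manipulation checks as "Memory Support Rating Scale (Total amount; Number of types)".
- **Use of the observer count.** Manipulation check plans independent-samples t-tests of whether the amount of constructive support, the number of types and "patient recall will be greater in the TranS-C + MSI condition compared to TranS-C alone". No dose figure is attached.

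**The concern.** The article assigns two questions to two instruments, and the dose question goes to the weaker one. The checklist is unmasked self-report by therapists trained to the target, and its total is in different units from the target although the numbers look alike (0–12 against 10–12). The MSRS is masked and counts supports per session, but the only analysis stated for it asks whether one arm exceeds the other.

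Interpretation is what is at stake. If the primary result is null, readers will ask whether memory support does not help or was delivered below the intended amount. The article raises that question about its predecessor. A significant between-arm test does not settle it, and a summed band score cannot be set directly against 10–12.

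**Working it through.** **Number of coded sessions.** Sample size {14} takes 148 and adds 20%: 148 × 1.20 = 177.6, so 178, as stated. With 1:1 allocation and one session each, that is 178 / 2 = 89 coded sessions per arm. If only 148 were coded it would be 74.

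**1. The checklist score against true counts.** Every split of a true total over the four strategies was scored with the article's bands.

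| True supports in a session | Lowest score | Highest score |
|---|---|---|
| 6 | 3 (all in one strategy) | 5 (3+1+1+1) |
| 10 | 3 (all in one strategy) | 7 (3+3+3+1) |
| 12 | 3 (all in one strategy) | 8 (3+3+3+3) |

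In the other direction, a score of 3 fits 3 supports or any larger number, because the top band is open-ended. A score of 7 needs at least 10 supports (3+3+3+1). A score of 10 needs at least 18 (6+6+3+3). A reader who set the score directly against 10–12 would therefore call on-target sessions far short.

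Averaging over sessions helps only in part. Assume Poisson counts per strategy. The mean score is then about 3.9 at a mean dose of 6 and 6.1 at 11 when supports are spread evenly, so gross under-dosing would usually show. At dose 11 it falls to about 5.1 if 70% of supports sit in one strategy. A mean score of about 4.8 arises from dose 8 spread evenly and from dose 10 so concentrated.

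**2. The between-arm test.** The article gives no MSRS SD and no control mean. Assume a common SD of 2, 4 or 6, independent sessions and two-sided alpha 0.05.

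- Smallest significant difference = t × SD × √(2/n). With n = 89 this is 0.296 × SD; with n = 74 it is 0.325 × SD.
- Difference with 80% power = (1.96 + 0.84) × SD × √(2/89) = 0.42 × SD.

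| Assumed SD | Just significant, n = 89 | Just significant, n = 74 | 80% power, n = 89 | Memory support mean at 80% power if control mean is 2 |
|---|---|---|---|---|
| 2 | 0.59 | 0.65 | 0.84 | 2.84 |
| 4 | 1.18 | 1.30 | 1.68 | 3.68 |
| 6 | 1.78 | 1.95 | 2.52 | 4.52 |

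A true mean of 5 against a control mean of 2 is half of 10 and passes with power of about 100%, over 99% and 92% for the three SDs. If control therapists already average 4 and the SD is 6, the mean at 80% power is 4 + 2.52 = 6.52.

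**3. Therapist clustering.** Each therapist delivers one arm only (Treatment fidelity), and the number of therapists is not given. As an illustration, assume 5 per arm and an intraclass correlation of 0.2. The design effect is 1 + (89/5 − 1) × 0.2 = 4.36, and its square root is 2.09. A test that allowed for therapist would need about twice the differences above. With SD 4 and control mean 2, the mean at 80% power becomes 2 + 1.68 × 2.09 = 5.5. That is still well below 10, but much closer than 3.68.

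**4. What the same tapes give as an estimate.** The 95% CI half-width for the memory support mean is t × SD / √89 = 0.42, 0.84 or 1.26 for SD 2, 4 or 6. Under the clustering illustration these become about 0.9, 1.8 and 2.6, and somewhat wider with so few therapists.

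**The case against.** The article does plan a dose check, and separating the arms is a legitimate separate purpose for a manipulation check. The MSRS is also listed as a fidelity measure, and Treatment fidelity says it will assess how often and which kinds of support are used. The t-test yields the arm's mean count, so a low dose would be visible to anyone who looks. The checklist covers up to 8 × 89 = 712 sessions against 89 tapes, and the target is an average, not a per-session requirement. Patient recall is compared between arms as well and modelled as the mediator in Aim 2, which gives further evidence on whether the target was engaged.

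All of this stands, and it limits the point. A reader might infer that the trial has no check on dose, or that the manipulation check carries no information about it; the text supports neither. What remains is that the article names the checklist as the instrument for the dose question and gives the observer count no stated role there. This is a choice the article makes, not detail left to an unseen analysis plan. Recall does not close the gap, since weak recall could reflect either too few supports or supports that do not work.

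**Conclusion.** The concern holds in a limited form. The dose question is assigned to an unmasked, banded self-rating whose total is not in the units of the 10–12 goal. The masked count in those units has only a between-arm test, which requires no particular dose. The checklist mismatch follows exactly from the article's own bands: 10–12 true supports score 3 to 8, and 6 score 3 to 5.

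The size of the second part is conditional. A reader might infer that the t-test passes almost surely at about a third of the target. That needs small SDs, a low control mean and independent sessions, none of which the article states. The supportable claim is that significance is possible well below the target, by an amount the article does not allow one to fix.

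A reader might also conclude that the manipulation should count as confirmed only if the estimate reaches 10–12. The plan's own rationale argues against that: it calls the goal conservative, cites 8 to 12, and says most outcomes peaked below 10.

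The primary analysis and the sample size are untouched. The consequence is confined to how the result, especially a null one, is explained.

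**What to change.** In Fidelity checks and Manipulation check:

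1. Keep the between-arm MSRS t-test and describe it as a check that the arms were separated.
2. Pre-specify that the memory support arm's mean MSRS constructive count per session will be reported with a 95% CI allowing for therapist clustering, as the main evidence on delivered dose. Read it against the article's own figures, the 10–12 goal and the 8–12 range, with no pass/fail rule at 10.
3. Treat the provider checklist as supporting information, and state that its summed band score is not to be compared directly with 10–12.

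The cost is one additional estimate from tapes that will be coded anyway, plus a few sentences of text. The interval may be wide if there are few therapists.
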